#### Strategies for managing SAD recurrences following a first-line treatment are lacking

A long-term perspective on mood status in future winters reflects SAD’s recurrent nature, consistent with the central public health challenge to prevent recurrence. SAD’s predictable, seasonal course of onset and remission “uncouples” the treatment and prevention phases of randomized clinical trials spanning multiple years. Acute treatment response and recurrence are two different outcomes, both worthy of attention. Although the field lacks an accepted SAD “treatment failure” definition, we argue that recurrence is a more clinically meaningful benchmark than post-treatment non-remission status. It is inarguably a poor outcome if a SAD patient achieves post-treatment remission but develops a recurrence the next winter. Conversely, it is a favorable outcome if a SAD patient does not fully remit at treatment endpoint, but reinitiates LT or uses cognitive-behavioral strategies early the next year to prevent recurrence. No algorithms exist to guide clinicians when a patient recurs following a first-line SAD treatment. Even basic non-responder trials are scarce, with only a few small-scale SAD studies (Ns = 13–16) switching or augmenting with tryptophan following nonresponse to LT [39, 40].

### Objectives {7}

Our goal is to inform evidence-based guidelines for personalized medicine using CBT-SAD and LT, specifically for determining [1] which patients are best suited for which type(s) of treatment in terms of recurrence prevention, and [2] whether the selected treatment engages its intended target. We will ascertain whether theoretically derived candidate biomarkers of each treatment’s target and effect are prescriptive of better outcomes in that treatment vs. the other. We will examine the established chronobiological biomarker of LT’s target and effect, PAD, and explore the PIPR as a candidate biomarker of melanopsin-driven retinal subsensitivity with specificity to LT. We will use self-reported seasonal beliefs as the established target and mechanism of CBT-SAD and also map this construct onto theoretically relevant biomarkers of reduced emotional reactivity to seasonal stimuli, pupil dilation and sustained frontal gamma band EEG responses to seasonal words. In addition to determining whether these interventions engage associated change mechanisms, we will test the efficacy of a “switch” decision rule upon recurrence the next winter to inform clinical decision-making for managing SAD recurrences following a first-line treatment.

In this confirmatory efficacy R01, adults with SAD (target *N* = 160) will be randomized to two equal-probability 6-week treatment conditions in winter 1: CBT-SAD or LT. We will follow subjects in winter 2 and if a depression recurrence occurs, we will cross them over into the alternate treatment (i.e., switch to CBT-SAD upon recurrence after LT, switch to LT upon recurrence after CBT-SAD). All subjects will be assessed at follow-up in winter 3. Biomarker assessments will occur at pre-, mid-, and post-treatment in winter 1; at winter 2 follow-up (and again at mid- and post-treatment for those with depression recurrences crossed-over into the other treatment); and at winter 3 follow-up. This work will yield longitudinal data on targets, their engagement, and stability, thereby increasing the impact of future dissemination efforts.

Specific aims are:To confirm the superiority of CBT-SAD over LT on depression recurrence status (the primary outcome)To elucidate differential mechanisms of acute treatment effects in CBT-SAD vs. LT by examining candidate biomarkers as potential mediators and to assess whether biomarkers at baseline, changes during treatment, and stability of changes over time are predictive of acute and/or long-term outcomes (recurrences)To compare a switch to CBT-SAD for those who recurred after LT to a switch to LT for those who recurred after CBT-SAD. We expect that a switch from LT➔CBT-SAD will show advantage over a switch from CBT-SAD➔LT in depression recurrences at winter 3, based on prior findings for greater durability in CBT-SADTo examine mediators of the effect of CBT-SAD on outcomes at winter 2 and winter 3

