### Trial design {8}

This is a head-to-head confirmatory efficacy trial comparing CBT-SAD and LT (with equal-probability allocation) designed to test superiority of one treatment over the other in depression recurrences at winter 2 follow-up. Participants with recurrences at winter 2 follow-up will be offered the opportunity to cross-over into the alternate treatment. All participants are followed-up at winter 3 (Fig. 1).

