#### Light therapy (LT)

Participants attend an initial instructional session that follows a script to explain the treatment rationale and assembly/position of the light box. These will be conducted by the (unblinded) P.I. in small groups of 2–4 subjects for efficiency. Effective fall/winter of 2020–2021, the P.I. posted a video recording of the instructional session on the lab’s private YouTube channel for those randomized to light therapy to watch remotely, due to the COVID-19 pandemic. In their homes, LT participants will use the SunRay (SunBox Company, Gaithersburg, MD), a standard device (23” × 15½”× 3¼”) with an ultraviolet shield that emits 10,000-lux of cool-white fluorescent light to the retina when the user is within 18 inches. Each of the 6 weeks, participants will complete the Light Therapy Side Effects Questionnaire used in our prior studies to assess the presence and severity of any side effects attributed to LT and self-reported times for onset of sleepiness, onset/offset of actual sleep, and desired times for onset/offset of sleep over the previous week. Side effects associated with LT are generally mild and can include headache (19%), eyestrain (17%), and feeling “wired” (14%) [46]. Although individuals typically respond within 4 weeks of initiating LT or not at all [16], our LT protocol will be maintained for 6 weeks to match CBT-SAD’s duration. To circumvent ethical concerns of discontinuing LT during the winter (when relapse is likely) [1], participants are encouraged to keep using the light box and bring it to the lab for servicing in May (to check the bulbs against a photometer and download adherence data). In an effort to reduce access to a suitable device as a potential confound, we will offer access to our light boxes to LT participants in winters 2 and 3 and to CBT-SAD participants crossed into LT in winter 2 for use in winter 3.

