As a step to increase the likelihood that treatment in the interim is consistent with initial study treatment, we will use standardized procedures for instructing participants at the end of study treatment. The first week of September, we will mail standardized letters, signed by the PI, to all participants treated the winter before prompting them to resume study treatment and to pursue new treatments only if needed. Both the CBT-SAD and LT letters include the same, standardized safety net in providing contact information for local mental health centers and treatment providers should they require more formal treatment. The letter to CBT-SAD-treated participants encourages them to keep using the skills learned in the CBT-SAD treatment on their own (without a therapist). The letter to LT-treated participants encourages them to re-initiate daily LT upon onset of the first depressive symptom in the coming fall/winter by either [1] borrowing one of our light boxes or [2] purchasing a device. Should they wish to purchase their own light box, we provide contact information for LT manufacturers with a list of specifications to match our devices (i.e., full-sized units emitting 10,000-lux cool-white light through UV filter). For either scenario, we ask the participant to identify a professional to whom they could turn in the event of side effects (since we will no longer monitor side effects and make prescription adjustments, as we did during acute treatment). LT participants may choose whether or not to have the PI provide a signed, generic letter that the participant may submit to his or her health insurance company to seek reimbursement for the cost of a light box. Participants crossed from CBT-SAD to LT at winter 2 will receive the standard LT letter the next September (winter 3), and participants crossed from LT to CBT-SAD will receive the standard CBT-SAD letter the next September.

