To examine mechanistic differences between CBT-SAD and LT, mixed effects linear regression with subject as a random effect will be used to model biomarker changes during treatment as a function of time, treatment, and their interaction. We will also model the relationship between biomarker change and change depressive symptoms as a function of treatment by letting the regression coefficient differ between CBT-SAD and LT. This will provide a test of whether potential mediators of effect are treatment-specific. The predictive value of biomarkers at baseline, their pre-post treatment change, and the persistence of the change at follow-up will be examined using logistic regression (for post-treatment remission and winter 2 recurrence) and linear regression (for SIGH-SAD and BDI-II scores) with post-treatment and winter 2 outcomes as dependent variables. Interactions between the biomarkers and treatment will be used to test if the associations with outcomes differ in the CBT-SAD and LT groups. Adherence will be included in ancillary analyses to test its effect on the relationships of treatment with biomarkers and LT or CBT-SAD outcomes. The relationships between biomarkers and outcomes will be validated by examining how well they predict post-treatment and winter 3 outcomes for subjects who experience a recurrence at winter 2 and are switched to the alternative treatment. Data from the cross-over subjects will also be analyzed using mixed linear regression to compare within-person differences in pre-treatment biomarkers and their changes during their initial and subsequent treatments. Treatment, time point (winter 1 or 2), and their interaction will be included to test the effect of treatment sequence on within-person differences in biomarker responses to CBT-SAD and LT.

##### Aim 3

Logistic and linear regressions similar to those for Aim 1 will be used to compare the effect of switching from CBT-SAD➔LT versus LT➔CBT-SAD on winter 3 recurrence and depression scores. Post hoc adjustment for any differences between switch groups in baseline characteristics, treatment response, and biomarker profiles will be done by including them as covariates. Mixed linear regression will be used to longitudinally model depression scores over the three winters, with treatment as a time-varying covariate.

##### Aim 4

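### The trial compares two switch sequences after recurrence and cannot test the efficacy of a switch rule; the light status of LT participants moved to CBT-SAD is also left unclear

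*Protocol article*

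**What the plan says.** **Objective.** Objectives {7} promises that "we will test the efficacy of a “switch” decision rule upon recurrence the next winter to inform clinical decision-making". The Abstract (Background) makes the same promise.

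**Assignment of recurrers.** Objectives {7}: "if a depression recurrence occurs, we will cross them over into the alternate treatment". Trial design {8} words it as an offer: "Participants with recurrences at winter 2 follow-up will be offered the opportunity to cross-over into the alternate treatment". No section assigns a recurrer to continue or repeat the first treatment.

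**Aim 3.** The specific aim is "To compare a switch to CBT-SAD for those who recurred after LT to a switch to LT for those who recurred after CBT-SAD". The Aim 3 analysis will "compare the effect of switching from CBT-SAD➔LT versus LT➔CBT-SAD on winter 3 recurrence and depression scores". Sample size {14} gives power for that same contrast: 37 LT and 22 CBT-SAD recurrers, with 80% power for 60% versus 25%.

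**Light after winter 1.** The Light therapy (LT) section states "we will offer access to our light boxes to LT participants in winters 2 and 3". The same sentence goes on to include people moved from CBT-SAD to LT, for winter 3, but says nothing of people moved the other way. Under Provisions for post-trial care {30}, the September letter asks LT participants to restart daily light once symptoms begin, with a borrowed or bought box. For the following year, "participants crossed from LT to CBT-SAD will receive the standard CBT-SAD letter the next September".

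**Biomarkers.** The Aim 2 analysis of cross-over participants will "compare within-person differences in pre-treatment biomarkers and their changes during their initial and subsequent treatments". Its model terms are treatment, winter and their interaction.

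**The concern.** The protocol's section on managing recurrences says clinicians have no algorithm when a patient recurs after a first-line treatment. Their question is whether to switch or to persist. A stated test of a switch rule will be read as answering it, yet the design has no group from which the result of persisting could be estimated.

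Recurrers are defined by SIGH-SAD thresholds (total at least 20, with HAM-D and atypical minimums) at one January assessment. People selected on a high score at one time tend to score lower at the next, and SAD severity may vary between winters. Some would not meet the criteria in winter 3 whatever was done in winter 2. The documents give no data from which to size this.

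The light question affects what the LT-to-CBT-SAD sequence is. If some in it continue light, their winter 3 result reflects CBT-SAD plus light. If some were on light when the January biomarkers were taken, the baseline for their second treatment carries an effect of the first, most directly on phase angle difference, the established LT marker.

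**Working it through.** **1. Reproduce the plan's figures.** Prior recurrence rates (Background {6a}) are 45.6% after LT and 27.3% after CBT-SAD, with 80 per arm.
- LT recurrers: 80 × 0.456 = 36.5, stated as 37.
- CBT-SAD recurrers: 80 × 0.273 = 21.8, stated as 22.

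Power for 60% (n = 22) versus 25% (n = 37), unpooled normal formula. The article gives no alpha, so two-sided 0.05 is assumed:
- SE = √(0.60×0.40/22 + 0.25×0.75/37) = √(0.01091 + 0.00507) = 0.1264
- 0.35/0.1264 − 1.96 = 0.81, so power is 79.1%

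The stated 80% is reproduced. Other formulas give 77.1% (pooled), 76.8% (arcsine) and 71.3% (Fisher exact). With 20% attrition (17.6 and 29.6) and 39 points, the unpooled formula gives 79.9–80.0%, again as stated.

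**2. What that power is for.** Both figures concern one direction of switch against the other. No figure in the document concerns switching against continuing, because no such contrast exists. Cross-over is an offer, so decliners may exist, but they select themselves and are not an assigned control.

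**3. The Aim 3 groups are not randomised groups.** They are formed by recurrence after randomisation, an outcome the trial expects to differ by arm (37 versus 22). The analysis provides post hoc covariate adjustment for differences between them.

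**4. Light at the winter 2 baseline.** LT participants are told in September to restart light when symptoms begin. By the January assessment every LT recurrer is symptomatic. If a fraction *f* is using light, 37 × *f* participants have a second-treatment baseline taken under light.
- *f* = 0.41, the general continuation rate in Background {6a}: 37 × 0.41 = 15.2
- Possible range: 0 to 37, with each 10 percentage points of *f* moving it by 3.7

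The 41% describes everyone treated acutely with LT, not recurrers. Loaned boxes could raise use among recurrers, while people who did not restart may be over-represented among them.

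**5. Can the Aim 2 terms separate this?** The cross-over data have four treatment-by-winter cells: LT-1 and CBT-2 (LT first), CBT-1 and LT-2 (CBT-SAD first). Suppose light use shifts the mean of CBT-2 by δ. With equal weights:
- Treatment: (CBT-1 + CBT-2)/2 − (LT-1 + LT-2)/2 shifts by δ/2
- Winter: (CBT-2 + LT-2)/2 − (LT-1 + CBT-1)/2 shifts by δ/2
- Interaction (sequence): (LT-1 + CBT-2)/2 − (CBT-1 + LT-2)/2 shifts by δ/2

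The shift spreads over all three terms, and the treatment term is not protected by having the interaction in the model. The size of δ is unknown.

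**6. Light status after cross-over.** The Light therapy (LT) section offers boxes to LT participants in winter 3 and makes no exception for those crossed out, although cross-over in the other direction is named in that sentence. Provisions for post-trial care {30} treats the same people as CBT-SAD for winter 3. No section says what happens to light or to the box at cross-over.

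**The case against.** **The operative plan makes no switch-versus-continue claim.** The specific aim, power and analysis all compare directions of switch. This stands, and it places the fault in the Abstract and the Objectives narrative, not in Aim 3 as worded. Having no arm that continues is a design choice. The error is describing the design as a test of the rule.

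**Device access and letters are different things.** The two provisions are not a flat contradiction, and a condensed article may leave detail out. That limits the point to a clarification, but it is still needed because the sentence on boxes deals with cross-over in one direction only.

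**Concurrent light is partly handled.** Aim 1 adjusts in some analyses for light used by the CBT-SAD group, and Aim 3 uses similar regressions. Interim treatment use is collected at follow-up, adherence enters ancillary Aim 2 analyses, and outside treatment begun during study treatment is recorded. This stands in part. The question asked at each SIGH-SAD is about newly started treatment, which need not capture someone continuing light. Nothing expressly extends the adjustment to crossed LT participants or to the within-person biomarker model.

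**Stronger readings that a reader might infer, and that the documents do not support:**
- That the authors' prior study showed the combination to differ from CBT-SAD alone. The section on choice of comparators reports each against LT at follow-up, gives no direct comparison of the two at that time, and reports no significant difference among active treatments acutely.
- That Aim 2 treats both winter 2 baselines as untreated. It calls them pre-treatment, allows them to differ within person and includes a sequence term. The problem is only that its terms do not isolate light use.
- That LT-to-CBT-SAD is in fact augmentation. The CBT-SAD letter for winter 3 points the other way, so it is only possible. Carry-over can also run in the other direction, through CBT-SAD skills retained during LT.

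**Conclusion.** The concern holds in limited form. The trial can compare two second-line sequences among recurrers, with the limits of a non-randomised comparison. It cannot show that switching is better than continuing, so the wording in the Abstract and Objectives {7} overstates what Aim 3 yields. This is a fact of the design and does not depend on any power calculation. It touches all of the roughly 59 projected switchers (37 + 22) but not the primary winter 2 comparison.

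The light issue is secondary. It concerns the 37 projected LT-to-CBT-SAD participants. How many have a biomarker baseline under light is unknown, and 15 is only what the general 41% rate would give. The passages on light boxes and letters must be reconciled; which rule applies is for the sponsor.

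**What to change.** 1. In the Abstract and Objectives {7}, restate the objective as a comparison of two second-line treatment sequences after recurrence. State that no conclusion on switching versus continuing will be drawn.
2. Reconcile the Light therapy (LT) section with Provisions for post-trial care {30}, so that the intended light status of LT participants crossed to CBT-SAD is explicit.
3. In the Aim 2 within-person model, account for light use at the winter 2 baseline, from the logger where a study box is in use and otherwise from the interim treatment-utilisation questionnaires.
4. In Aim 3, describe or adjust for continued light within the LT-to-CBT-SAD group only, as a sensitivity analysis in line with the Aim 1 covariates. Light use during the second treatment or in winter 3 should not be a covariate across both switch groups: it is the assigned treatment in CBT-SAD-to-LT, and adjusting for it would remove much of the contrast being tested.

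The cost is wording, one clarified provision and analyses of data already planned for collection. The downside is a narrower Aim 3 claim and small, self-selected subgroups by light use, which can support description more than inference.

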### Trial design {8}

This is a head-to-head confirmatory efficacy trial comparing CBT-SAD and LT (with equal-probability allocation) designed to test superiority of one treatment over the other in depression recurrences at winter 2 follow-up. Participants with recurrences at winter 2 follow-up will be offered the opportunity to cross-over into the alternate treatment. All participants are followed-up at winter 3 (Fig. 1).

**Fig. 1 Fig1:**
[figure not shown]
Anticipated participant flow in the randomized clinical trial

## Methods: participants, interventions, and outcomes

### Study setting {9}

This is a single-site trial taking place in the principal investigator’s (K.J.R.) mood disorders and seasonality research laboratory at the University of Vermont, Department of Psychological Sciences, Burlington, VT, USA.

### Eligibility criteria {10}

We will use the same inclusion/exclusion criteria from our previous R01 clinical trial, as they balance rigor and relevance for community samples and yielded a sample of the proposed size. Inclusion criteria are as follows: (a) principle DSM-5 diagnosis of Major Depression, Recurrent, with Seasonal Pattern on the Structured Clinical Interview for DSM-5 Axis I Disorders— Research Version (SCID-5-RV) [41], (b) meet Structured Interview Guide for the Hamilton Rating Scale for Depression—Seasonal Affective Disorder Version (SIGH-SAD) [42] criteria for a current SAD episode (total score ≥ 20 and ≥ 5 on the 8-item atypical subscale), and (c) no use or stable use of antidepressants (i.e., a consistent dose of the same medication maintained for ≥ 4 weeks with no plans to change), and (d) medical clearance to participate on the basis of physical exam/medical work-up at the University of Vermont Clinical Research Center (CRC). [Note regarding (c): In the last R01 study, 25.4% of subjects were taking antidepressants at baseline, and only 1 subject reported a medication change during treatment]. Exclusion criteria are as follows: (a) current or past LT or CBT for SAD, (b) current or past bipolar disorder or psychotic disorder, (c) current substance use disorder beyond mild severity, (d) acute and serious suicidal intent, (e) planned absences of > 1 week from the area during the projected treatment interval, (f) history of conditions that are known contra-indications to LT, including conditions associated with toxicity of bright light to the retina (i.e., macular degeneration or any retinopathy), (g) photosensitizing reaction to any current medication (e.g., rash upon exposure to sunlight); and (h) positive laboratory findings for hypothyroidism at medical screening/work-up visit.

#### Screening and enrollment procedures

Participants will be recruited from media advertisements, referrals from local physicians and mental health clinics, and community outreach. Interested volunteers will undergo a brief phone screening to assess basic inclusion/exclusion criteria, including assessment of major depressive episode criteria for the previous winter. Those who appear eligible will be invited to review the informed consent form, and if they consent to the study, to proceed with diagnostic interview, the Structured Clinical Interview for DSM-5 Axis I Disorders—Research Version (SCID-5-RV) [41], administered by the P.I. or a trained clinical psychology graduate student research assistant. If the SCID diagnosis is Major Depressive Disorder, Recurrent, with Seasonal Pattern (inclusion criterion a) and there are no comorbid disorder exclusions (exclusion criteria b and c); the participant will be asked to attend the medical screening/work-up where they will undergo a physical examination and medical chart/history review with a physician assistant, vital signs are collected (blood pressure, pulse, height, and weight), and blood is drawn for thyroid panel (TSH, and free T4). If no medical exclusion is identified (inclusion criterion d and no documented evidence of exclusion criteria b, c, or f on the basis of medical record review), the participant enters the symptom monitoring phase of the study. The SIGH-SAD will be administered by a trained research assistant every other week until SIGH-SAD criteria for a current SAD episode (inclusion criterion b) are met. When a potential participant meets SIGH-SAD criteria for a current SAD episode, they will be asked to attend the pre-treatment assessment, at the conclusion of which, the participant is actively enrolled and randomized. After the first week of February, SIGH-SADs will be discontinued for any potential participant not meeting threshold for a SAD episode because: (1) in our experience, after this date, there is low likelihood of developing a full threshold episode in that winter, and (2) insufficient time remains to ensure completion of the pre-treatment assessment procedures and the 6-week treatment phase before the possibility of spontaneous springtime remission.

